# Safety and efficacy in pediatric secondary intraocular lens implantation, in-the-bag versus sulcus implantation: a multicenter, single-blinded randomized controlled trial

**DOI:** 10.1186/s13063-023-07411-z

**Published:** 2023-06-09

**Keywords:** Pediatric aphakia, Secondary intraocular lens implantation, Glaucomarelated, Adverse events, In-the-bag IOL implantation, Sulcus IOL implantation

## Abstract

**Background:**

Treatment of pediatric cataract remains challenging because of the extremely high incidence of postoperative adverse events (AEs), especially the AEs related to the locations of secondary implanted intraocular lens (IOL). There are two common locations for secondary IOL implantation in pediatric aphakic eyes: ciliary sulcus or in-the-bag implantation. However, there are currently no large, prospective studies comparing complication rates and visual prognosis of in-the-bag versus ciliarysulcus secondary IOL implantation in pediatric patients. Whether or how much secondary in-the-bag IOL implantation benefits the pediatric patients more than sulcus implantation and deserves to be performed routinely by surgeons remains to be elucidated. Here, we describe the protocol of a randomized controlled trial (RCT) designed to evaluate the safety and efficacy of two approaches of IOL implantation in pediatric aphakia.

**Methods:**

The study is a multicenter, single-blinded RCT with 10 years of follow-up. Overall, a minimum of 286 eyes (approximately 228 participants assuming 75% have two study eyes) will be recruited. This study will be carried out in four eye clinics across China. Consecutive eligible patients are randomized to undergo either secondary in-the-bag IOL implantation or secondary sulcus IOL implantation. Participants with two eyes eligible will receive the same treatment. The primary outcomes are IOL decentration and the incidence of glaucoma-related AEs. The secondary outcomes include the incidence of other AEs, IOL tilt, visual acuity, and ocular refractive power. Analysis of the primary and secondary outcomes is to be based on the intention-to-treat and per-protocol analysis. Statistical analyses will include the *χ*^2^ test or Fisher’s exact test for the primary outcome, mixed model and generalized estimated equation (GEE) model for the secondary outcome, Kaplan–Meier survival curves for the cumulative probability of glaucoma-related AEs over time in each group.

**Discussion:**

To the best of our knowledge, this study is the first RCT to evaluate the safety and efficacy of secondary IOL implantation in pediatric aphakia. The results will provide high-quality evidence for the clinical guidelines for the treatment of pediatric aphakia.

**Trial registration:**

ClinicalTrials.gov NCT05136950. Registered on 1 November 2021.

## Introduction

### Background

Treatment of pediatric cataract, one of the leading causes of childhood blindness globally, remains challenging because of the extremely high incidence of postoperative adverse events (AEs) [1–4]. Especially, the AEs related to the locations of secondary implanted IOL, such as iris-related inflammation, glaucoma-related AEs, and IOL positional stability potentially affect patients’ prognosis [5–9].

Theoretically, in-the-bag implantation of IOL prevents contact with the iris and may reduce the risk of AEs [10, 11]. However, due to the difficulties in performing secondary in-the-bag implantation in pediatric aphakic eyes, secondary IOL implantation with ciliary sulcus fixation in these patients is considered acceptable [12–15].

We and other investigators have demonstrated high feasibility of secondary in-the-bag IOL implantation in pediatric aphakic eyes [1, 7, 16–19]. In our prospective comparative study of 355 pediatric eyes undergoing secondary IOL implantation, we investigated the 3-year outcomes of these two methods and found that compared to ciliary sulcus secondary IOL implantation, in-the-bag IOL implantation reduced AEs and yielded better IOL centration and best corrected visual acuity (BCVA) for pediatric aphakia [1]. However, there have been no large, prospective cohort studies adjusting for important determinants of AEs and comparing outcomes of in-the-bag versus ciliary-sulcus secondary IOL implantation.

Whether or how much secondary in-the-bag IOL implantation benefits the pediatric patients more than sulcus implantation and deserves to be performed routinely by surgeons remains to be elucidated.

### Objectives

#### Main objective

The main objective is to compare the safety of in-the-bag versus ciliary-sulcus secondary intraocular lens (IOL) implantation in pediatric aphakia, including IOL decentration and the incidence of glaucoma-related adverse events.

#### Secondary objective

The secondary objective is to compare the efficacy of in-the-bag versus ciliary-sulcus secondary intraocular lens (IOL) implantation in pediatric aphakia, including the incidence of other adverse events, IOL tilt, visual acuity (VA), and ocular refractive power.

## Methods

### Trail design

This protocol follows the Standard Protocol Items for Clinical Trials (SPIRIT 2013) [20]. The study flow chart is shown in detail in Fig. 1.AStudy design: prospective, multicenter, superiority, parallel-group, single-blinded, and randomized controlled trialBIntervention groups: consecutive eligible patients are randomized to undergo either secondary in-the-bag IOL implantation (capsular group) or secondary sulcus IOL implantation (sulcus group)

**Fig. 1 Fig1:**
[figure not shown]
Study flow chart

Study participants may have one or two study eyes. Study participants with two study eyes eligible will receive the same treatment. Further details on randomization are located in the “Randomization” section.

For both intervention groups, the surgeries are described in the “Interventions” section.CSample sizeA minimum of 286 eyes (approximately 228 study participants assuming 75% have two study eyes)DDuration of follow-upPrimary outcome: 1 yearTotal follow-up: 10 yearsEFollow-up scheduleYears 1: follow-up visits occur 1 day, 1 week, 1 month, 3 months, 6 months, and 1 year postoperativelyYears 2 to 10: follow-up visits occur every 6 months

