### Sample size

According to the Zhongshan Ophthalmic Center’s outpatient record system, (1) the one-year incidence of glaucoma-related AEs in sulcus implantation is 12%. Assuming the in-the-bag implantation would reduce the absolute incidence to 0.7%, to achieve 90% power with a two-sided alpha of 0.0492 (the interim analysis at 6 months postoperatively spending alpha of 0.0054 by O’Brien-Fleming approach), 114 eyes are needed for each group (total of 228 eyes) using Fisher’s exact test with pooled variance. Allowing for a 20% loss to follow-up, 143 eyes should be needed in each group. Assumptions: % of bilateral = 75%, inter-eye correlation among bilateral patients = 0.5. For bilateral patients, two eyes have the same type of surgery. The number of patients (*X*) per group can be calculated by solving the following equation: *X* × 0.75 × 2/(1 + 0.5) + *X* × 0.25 = 143, *X* = 114 patients per group, a total of 228 patients. The sample size is calculated by PASS 16.0 (NCSS, LLC, USA). (2) IOL decentration in 3-dimension in the capsular group is 0.38 mm while in the sulcus group, it is 0.56 mm. Group sample sizes of 106 and 106 achieve 90% power to detect the mean difference of 0.18 between two trial arms with a common standard deviation for both groups of 0.40 and with a two-sided alpha of 0.0492 using a two-sided two-sample equal-variance *t*-test (same interim analysis as above for the 1-year incidence of glaucoma-related AEs). Allowing for a 20% loss to follow-up, 133 eyes should be needed in each group. Assumptions: % of bilateral = 75%, inter-eye correlation among bilateral patients = 0.5. For bilateral patients, two eyes have the same type of surgery. The number of patients (*X*) per group can be calculated by solving the following equation: *X* × 0.75 × 2/(1 + 0.5) + *X* × 0.25 = 133, *X* = 106 patients per group, a total of 212 patients. The sample size is calculated by PASS 16.0.

Considering the sample size calculated by the two primary outcomes, the largest one is selected: 114 patients per group, a total of 228 patients.

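### The stated minimum of 286 eyes is a count of independent-equivalent eyes; the 228 participants printed beside it would bring about 399 real eyes

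*Protocol article*

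**What the plan says.** The Abstract (Methods) says that "a minimum of 286 eyes (approximately 228 participants assuming 75% have two study eyes) will be recruited". Item C of the trial design section gives the same pair of figures: a "minimum of 286 eyes (approximately 228 study participants assuming 75% have two study eyes".

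The Sample size section shows where the numbers come from. For glaucoma-related events it takes 12% with sulcus implantation and 0.7% in the bag, and it aims "to achieve 90% power with a two-sided alpha of 0.0492". It concludes that "114 eyes are needed for each group (total of 228 eyes) using Fisher’s exact test with pooled variance". It continues: "Allowing for a 20% loss to follow-up, 143 eyes should be needed in each group". Twice 143 is 286. The section then converts eyes to children, assuming 75% bilateral and an inter-eye correlation of 0.5. Its equation weights each bilateral child as 2/(1 + 0.5) and each unilateral child as 1. A parallel calculation for decentration gives 106 per group before loss, 133 after, and 212 patients. The larger requirement is adopted: "114 patients per group, a total of 228 patients".

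**The concern.** The number 286 carries two meanings. In the Sample size section it is a statistical quantity: the independent eyes that would give the required information. In the Abstract and the design section it is a number of eyes to be recruited. With two correlated eyes in three quarters of the children, these quantities differ by more than 100 eyes.

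This matters because the two summary statements lead with eyes and call that figure the minimum, while the participant count follows as an approximation. A team that tracks recruitment in eyes would meet the stated minimum about 65 children short of the number that the Sample size section selects.

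**Working it through.** **Inputs (all from the Sample size section):** event rates 0.12 and 0.007; decentration difference 0.18 mm with SD 0.40; two-sided alpha 0.0492; power 90%; loss 20%; 75% bilateral; inter-eye correlation 0.5.

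**1. Reproducing the plan's figures**
- Glaucoma-related events, pooled-variance formula: n = [1.967·√(2 × 0.0635 × 0.9365) + 1.282·√(0.12 × 0.88 + 0.007 × 0.993)]² / 0.113² = 96.2. With the continuity correction, n/4 × [1 + √(1 + 4/(n × 0.113))]² = 113.2, which rounds up to the printed 114.
- Loss: 114/0.8 = 142.5, rounded up to 143 per group, so 286 in total.
- Effective eyes per child: 0.75 × 2/1.5 + 0.25 = 1.25. Then 143/1.25 = 114.4, printed as 114 per group and 228 in total.
- Decentration: 106 per group gives power 0.902 by the two-sample t-test. After loss this is 133, and 133/1.25 = 106.4, printed as 106 per group and 212 in total.

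The chain reproduces. No step before the 143 allows for two eyes in one child, and the correlation enters only in the conversion to children. So 286 is a count of independent-equivalent eyes.

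**2. Real eyes from 228 participants**
- Real eyes per child: 0.75 × 2 + 0.25 × 1 = 1.75.
- 228 × 1.75 = 399 real eyes.
- 228 × 1.25 = 285 effective eyes.
- For 228 children to supply 286 real eyes, the bilateral share would have to be 286/228 − 1 = 0.254, not 0.75.

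**3. If recruitment closed at 286 real eyes**
- Participants: 286/1.75 = 163.4, about 65 fewer than 228.
- Effective eyes: 163.4 × 1.25 = 204.3, or 102 per group.
- After 20% loss: 102.1 × 0.8 = 81.7, about 82 per group.

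| Outcome and method | Planned n per group | Power at planned n | Power at 82 per group |
|---|---|---|---|
| Glaucoma-related events, exact Fisher (enumerated) | 114 | 0.957 | 0.838 |
| Glaucoma-related events, continuity-corrected formula | 114 | 0.902 | 0.758 |
| Decentration, two-sample t-test | 106 | 0.902 | 0.815 |

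**4. Sensitivity at 286 real eyes**
- No loss at all (102 per group): 0.93 by exact Fisher, 0.86 continuity-corrected, 0.89 for decentration.
- 20% loss, correlation 0, 0.25, 0.5, 0.75 and 1: exact Fisher 0.96, 0.91, 0.84, 0.76 and 0.68; decentration 0.92, 0.87, 0.82, 0.76 and 0.72.

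**5. Is 114 per group enough?** 114 × 1.25 × 0.8 = 114.0 effective eyes per group after loss, exactly the requirement. For decentration, 106 × 1.25 × 0.8 = 106.0.

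**The case against.** The strongest reply is that nothing is lost in practice. The Sample size section ends by selecting 228 patients, both summary statements print 228 beside the eye count, and 286 is called a minimum, which 228 children at 75% bilateral would exceed. No passage makes 286 eyes a rule for stopping recruitment. This stands. A reader might infer that the trial is underpowered as planned, but the document does not support that: enrolling 228 keeps the planned size, and the power loss arises only if recruitment closes on the eye count.

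A second fair point concerns size. The test named for this outcome is Fisher's exact test (or χ²), so 84% describes the planned analysis better than 76%. The lower figure comes from the approximation that explains the printed 114, and it understates Fisher power at both sample sizes. The shortfall also depends on the planning values for loss and correlation. At a correlation of 0.25 the Fisher power would still be about 91%.

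A reader might also infer that 114.4 was wrongly rounded down and that 115 per group are needed. That does not hold. The 143 was itself rounded up from 142.5, and 142.5/1.25 is exactly 114.

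None of this removes the contradiction. The gap between 286 and 399 eyes follows from the 75% in the same parenthesis and needs no assumption about correlation or loss. A gap of 113 eyes is too large for a word such as approximately to cover.

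**Conclusion.** The sample size statement is wrong as written in the Abstract and in item C of the trial design section, where an independent-equivalent count is presented as a count of eyes to recruit. That much is exact arithmetic on the document's own figures. The participant target of 228 is sound under the plan's assumptions.

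The consequence for power is conditional. It applies only if recruitment closed at 286 real eyes, and its size rests on 75% bilateral, a correlation of 0.5 and 20% loss. In that case both primary outcomes would fall below the stated 90%. This is a correction worth making to the two statements, not evidence of a design that is too small.

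**What to change.** In both places, state the target in participants, for example: 228 participants (114 per group), about 399 study eyes if 75% have two study eyes, equivalent to about 285 independent eyes at an inter-eye correlation of 0.5. Delete 286 as a count of recruited eyes. In the Sample size section, label the 143 and 133 per group as independent-equivalent eyes so that the two meanings are not confused again.

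The cost is one sentence in each of two places and a label in a third. No children are added beyond the 228 already planned. If recruitment did close at 286 real eyes, the report should restate the power: about 84% by exact Fisher for glaucoma-related events and about 82% for decentration under the planning assumptions.

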### Study setting

This study will be carried out in four eye clinics across China, including (1) Zhongshan Ophthalmic Center (ZOC), Sun Yat-sen University; (2) Hainan Eye Hospital, Zhongshan Ophthalmic Center, Sun Yat-sen University (HNZOC); (3) the First Affiliated Hospital of Guangxi Medical University; and (4) Shenzhen Eye Hospital.

### Informed consent

On attending the screening clinic, potentially eligible participants and their parents (or legal guardians) will be approached by a trained research coordinator to determine whether they want to participate in the trial. If they express their interest, the researcher will gain informed consent and recruit the patient. Written informed consent will be obtained from the parent or legal guardian before performing the standard clinical surgical treatment. Once the patient is enrolled in the study, he/she will be assigned to either the capsular group or the sulcus group. When the participants reach 18, they should re-consent.

### Study participant eligibility criteria

Patients will need secondary IOL implantation if all the following findings and conditions are met:Age over 18 months for unilateral aphakia and over 24 months for bilateral aphakiaAxial length falls within the mean plus or minus two standard deviations of the age-matched healthy counterpartsCorneal diameters between 9.5 and 12.5 mm

#### Inclusion criteria

Patients of either gender will be eligible for the study if all the following findings and conditions are met:Aged between 18 months and 14 yearsHad a primary diagnosis of congenital cataractUnderwent unilateral or bilateral cataract extraction between the ages of 2 and 24 monthsPediatric eyes with sufficient space of anterior segment and volumized Soemmerring’s ring

#### Exclusion criteria

Patients will be excluded from the study if they meet any of the following criteria:Primary IOL implantationPre-existing ocular disease which might affect the location and outcome of secondary IOL implantation (including and not restricted to microphthalmia, microcornea, microcornea, corneal opacity, pseudopterygium, iris anomaly, glaucoma diagnosed before cataract extraction, uveitis, persistent fetal vasculature or trauma)Suture fixation for secondary IOL implantation

### Interventions

Participants will be randomly divided into two arms in a 1:1 ratio. Surgery in two arms will be performed by qualified surgeons using the standard operating procedure of IOL implantation [1, 16].

After a conjunctival peritomy is made, a 3.2-mm superior scleral tunnel incision will be created. Sodium hyaluronate will be used to maintain the anterior chamber. Then, surgery will proceed in the different groups as per random allocation. All operations will be videotaped in their entirety.

#### Secondary in-the-bag IOL implantation (capsular group)

The Soemmerring’s ring will be reopened intraoperatively to remove proliferated lens material. After the capsular bag is reestablished with sodium hyaluronate, an IOL will be implanted into the peripheral capsular bag.

#### Secondary ciliary sulcus IOL implantation (sulcus group)

The Soemmerring’s ring will be reopened intraoperatively to remove proliferated lens material. Then, an IOL will be implanted into the ciliary sulcus.

The subsequent steps include (secondary) capsulorhexis of the posterior capsule, anterior vitrectomy, irrigation, and aspiration. The tunnel incision is sutured with 10–0 nylon sutures. All patients will be received subconjunctival dexamethasone (2 mg) before the surgery is completed.

#### IOL selection

IOL styles: the style of IOL used for capsular bag implantation is single-piece hydrophobic spheric monofocal IOL (SA60AT, Alcon Laboratories, America), and the style of IOL used for sulcus implantation is three-piece hydrophobic spheric monofocal IOL (AR40e, Sensar, America).IOL power: targeted postoperative refraction range from + 4 diopters to emmetropia will be recommended according to age at secondary IOL implantation and/or the ocular refraction of the contralateral eye.IOL power adjustment for sulcus implantation: When the predicted power is between 11.5 and 30D, a corresponding reduction of 0.50–2.50D is made for a ciliary sulcus implanted IOL according to the unpublished refractive data from our cohort.

#### Postoperative eyedrops regimen

The postoperative eyedrops regimen to be followed for each group is the same. Postoperatively, Tobradex eye drops (tobramycin 0.3%, dexamethasone 0.1%, Alcon) will be used 6 times per day, and Tobradex eye ointment (tobramycin 0.3%, dexamethasone 0.1%, Alcon) will be applied once per night for 2 weeks. From 2 weeks to 1 month postoperatively, the eye drops will be used 4 times per day. For the second postoperative month, the patient will be switched to pranoprofen eye drops 4 times per day (Senju Pharmaceutical Co., Ltd., Osaka, JP) [16]. The medication regimen will be adjusted in time according to the individual postoperative situation. For example, for pediatric patients with postoperative glaucoma, topical lowering intra-ocular pressure drops will be added after ruling out the contraindications of local medication.

### Criteria for discontinuing or modifying allocated interventions

The end point of the study is to reach 10 years of follow-up. If intraoperative AEs occur during the study, including hyphema, vitreous hemorrhage, iris or vitreous prolapse, and iatrogenic injury of iris and, participants will receive in-time treatment, and the follow-up will continue. The AEs will be reported to the researchers and the ethics committees as required indicating expectedness, seriousness, severity, and causality.

### Strategies to improve adherence to interventions

We will introduce the purpose of the study and the interventions in detail and actively respond to any questions, and the participants will be closely followed up and deal with adverse events in time if happened.

### Relevant concomitant care permitted or prohibited during the trial

All relevant treatments should be used under the judgment of the clinician. The reason and detailed usage of additional medication should be recorded on the CRF.

### Outcomes

#### Primary outcomes

The primary outcomes include IOL decentration and the incidence of glaucoma-related AEs by 1 year postoperatively.Glaucoma-related AEs are defined using the Infant Aphakia Treatment Study: “comprising ocular hypertension, pupil block, and glaucoma” [19].Ocular hypertension is defined as intraocular pressure (IOP) ≥ 21 mm Hg.Transient ocular hypertension is defined as elevated IOP which is resolved with cessation of topical steroids. Cases which do not resolve are classified as persistent ocular hypertension.Pupil block is defined as ocular hypertension in the context of a history of obstruction of aqueous flow through the pupil.Glaucoma is defined using the 2001 British Infantile and Childhood Glaucoma (“BIG eye”) study group taxonomy: “the presence of a combination (more than one) of clinical signs consistent with high intraocular pressure (≥ 21 mmHg), such as high pressure, optic disc cupping ≥ 0.3 or disc asymmetry ≥ 0.2, progressive disc cupping, buphthalmos, enlarged corneal diameter, corneal edema, Descemet’s membrane splits/Haab’s striae, visual field defects, or progressive myopia.IOL decentration will be measured using anterior segment optical coherence tomography (AS-OCT, CASIA2, Tomey Corporation, Japan) or Scheimpflug tomography (Pentacam HR 70900, Oculus GMbH, Germany) as previously described [21]. The details can be found in the “Testing procedures” section.

#### Secondary outcomes

The secondary outcomes include the following:Incidence of glaucoma-related AEs by 6 months, 3 years, 5 years, and 10 years postoperativelyIOL decentration by 6 months, 3 years, 5 years, and 10 years postoperatively.Incidence of other AEs by 6 months, 1 year, 3 years, 5 years, and 10 years postoperatively. Other AEs include IOL dislocation, iris synechia, corectopia and/or discoria, visual axis opacification, corneal endothelium decompensation, and retinal detachment. It will be recorded separately using criteria previously reported [22, 23].IOL tilt by 6 months, 1 year, 3 years, 5 years, and 10 years postoperatively.VA and ocular refractive power by 6 months, 1 year, 3 years, 5 years, and 10 years postoperatively.

### Participant timeline

The time schedule for enrollment, interventions, assessments, and visits for the participants is summarized in Table 1.

**Table 1 Tab1:** The schedule of enrollment, interventions, and assessments

Time point	Study period							
	**Enrollment**	**Baseline visit**	**Intervention**	**Follow-up visits**				**Close-out**
	*** − t***_**1**_	***t***_**1**_		***t***_**2**_	***t***_**3**_	***t***_**4**_	**etc**	***t***_**25**_
